### Intervention

2.6

Besides the intervention described below, all participants are requested to continue their normal life and continue their treatment (ie, medication) during the trial. The intervention period starts on September 23, 2019, and ends on December 13, 2019.

#### Experimental group

2.6.1

To maximize transparency and replicability of the exercise protocol, we followed the guidelines stated on the Consensus on Exercise Reporting Template (CERT; Table S1).^[37]^ Participants assigned to the intervention group will carry out 2 strength training sessions weekly for 12 weeks. These 12 weeks are divided into 2 phases: a first phase of individual training (ie, 1:1 ratio) with a duration of 2 weeks and a second phase of 10 weeks in which group (ie, 4–6 participants) workouts are performed. Therefore, the program comprises a total of 24 training sessions (ie, of 60 minutes duration). In addition, the participants will be requested to undertake home-based aerobic training consisting in meeting the physical activity guidelines of 10,000 steps per day.^[39,40]^ The compliance with this requirement will be monitored through the Z11 Smart Band (Smart&Sport, Shenzhen, China) activity bracelet. The supervised training sessions will be led by exercise professionals (i.e. personal trainers; PT) with a degree in Physical Activity and Sport Sciences and with specific training in exercise for breast cancer patients. The exercise program will be carried out in a fitness room at the Almeria town hall (400 m^2^), which is equipped with aerobic and resistance training areas. The detailed description of the exercise equipment to be used during the training program is presented as additional file (Table S2).

Table 1 summarizes the periodization of the resistance training program. During phase 1 (ie, weeks 1 and 2; individual sessions), each participant will perform a total of 4 sessions in which the exercise professional will determine individual needs and limitations (eg, shoulder mobility, pain, etc) and participants will learn basic movement patterns that will be required in the following phase. During phase 2 (ie, weeks 3–12; group sessions), the participants will undertake circuit training including mobility and stability exercises and resistance training. There will be several stations in which participants will perform an exercise before moving to the next station. The starting level of each participant will be set considering their baseline muscular strength and the work undertaken in weeks 1 and 2.

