### Sample size

2.4

The sample size was calculated for the primary outcome (ie, muscular strength) using Stata v.13 (StataCorp LP, College Station, TX). Based on the results of the meta-analysis by Strasser et al,^[23]^ a difference in the change between groups in lower limb muscle strength of at least 6.9 kg would be clinically relevant. Assuming a common standard deviation of 7.5 kg, a 90% power, an alpha error of 5%, and considering a potential dropout of 20%, we will aim at enrolling 60 participants.

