### Statistical analysis

2.9

The distribution of the main study variables will be assessed through histogram and Q-Q plots. Descriptive characteristics will be presented using the mean and standard deviation for normally distributed quantitative variables, the median and interquartile range for non-normally distributed quantitative variables, and the number and frequency for categorical variables. The comparability of the groups will be checked at baseline and potential confounders that present baseline group differences will be included in the analyses. The between-group differences in the primary and secondary outcomes will be assessed through linear or quantile regression, as appropriate. As we aim at assessing efficacy, the primary analyses are defined as per-protocol, where participants from the exercise group will be included if their attendance to the exercise sessions is ≥75%. Sensitivity analyses will also be carried out using a minimum attendance of ≥90% and using the intention-to-treat principle. Blinded investigators ([name] and [name]) will handle all hypothesis testing. The main analyses will be conducted with Stata v.13.1 (StataCorp LP, College Station, TX). Statistical significance will be set at *P* < .05.

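### Exercise-arm women train in groups of 4-6 for 10 weeks, but the stated analyses do not address training group; if outcomes correlate within groups, intervals are modestly too narrow

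*Protocol article*

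**What the plan says.** Women are randomized individually by a simple computer-generated sequence (Protocol article, 2.5). The exercise arm has 2 weeks of one-to-one training, followed by "a second phase of 10 weeks in which group (ie, 4–6 participants) workouts are performed" (2.6.1). With two sessions a week, that makes 20 of the 24 sessions group sessions. Exercise professionals lead them. The control arm has a daily step target and no supervised training (2.6.2).

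On analysis, section 2.9 states: "The between-group differences in the primary and secondary outcomes will be assessed through linear or quantile regression, as appropriate". The primary analysis is per protocol, with at least 75% attendance required in the exercise arm. The sensitivity analyses listed are a 90% attendance threshold and intention to treat. Training group and trainer are not mentioned.

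The sample size (2.4) uses a difference of 6.9 kg and continues: "Assuming a common standard deviation of 7.5 kg", with 90% power and 5% alpha, and "considering a potential dropout of 20%, we will aim at enrolling 60 participants". It mentions no design effect.

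**The concern.** Delivering treatment to small groups in one arm only gives a partially nested design. Women who share a group also share a time slot, circuit sessions, a collective closing part and probably a coach. Their outcomes may therefore resemble each other more than those of women in different groups. An ordinary regression without a group term or cluster-adjusted errors counts each exercise-arm woman as a fully independent observation. If the within-group correlation is positive, it overstates the precision of the exercise-arm mean.

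At stake is a borderline result on strength. Its interval would be somewhat too short, and differences between groups or trainers could help carry it below P = .05. If group membership is not recorded, this cannot be checked afterwards.

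**Working it through.** **Inputs from the Protocol article.** Difference 6.9 kg, SD 7.5 kg, power 90%, alpha 5%, dropout 20%, total 60 (2.4); groups of 4-6 in the exercise arm only (2.6.1, 2.6.2); significance at P < .05 (2.9).

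**Assumptions.** Two-sided test; 1:1 allocation, so about 30 women per arm; ICC of 0, 0.02, 0.05 or 0.10. The ICC values are not in the documents.

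**Step 1: reproduce the plan's own figure.** For independent observations,

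n per arm = 2 × [7.5 × (1.960 + 1.282) / 6.9]² = 24.83, rounded up to 25.

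The total is 50, and 50 × 1.2 = 60. The stated 60 is reproduced with no allowance for clustering.

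**Step 2: groups as analysed.** Thirty women in groups of 4-6 make about 5-7 groups. With 20% loss, 30 × 0.8 = 24 women remain. Average group size falls to between 4 × 0.8 = 3.2 and 6 × 0.8 = 4.8. Six groups of 4 is a fair central case.

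**Step 3: effect of clustering in one arm.**

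- Exercise-arm design effect: DE = 1 + (m − 1) × ICC, with m = 4.
- Variance inflation of the difference, equal arms: VI = (1 + DE) / 2.
- Width of the correct interval relative to the ordinary one: √VI.
- Actual two-sided type I error of the ordinary test: 2 × [1 − Φ(1.96 / √VI)].

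| ICC (assumed) | DE | VI | Interval width | Type I error |
|---|---|---|---|---|
| 0 | 1.00 | 1.000 | × 1.000 | 5.0% |
| 0.02 | 1.06 | 1.030 | × 1.015 | 5.35% |
| 0.05 | 1.15 | 1.075 | × 1.037 | 5.9% |
| 0.10 | 1.30 | 1.150 | × 1.072 | 6.8% |

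Simulation of the ordinary t test (6 groups of 4 against 24 controls, 200,000 trials per setting) gave 5.0%, 5.2%, 5.8% and 6.8%. Taking formula and simulation together, about 5.3%, 5.9% and 6.7% is a fair summary for the three positive ICCs.

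**Step 4: larger groups.** A full arm of 5 groups of 6 with no loss has VI = 1.05, 1.125 and 1.25, which gives 5.6%, 6.5% and 8.0%. This is an upper case, because it ignores both dropout and the attendance rule.

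**Step 5: power.** With 24 evaluable women per arm, SE = 7.5 × √[(1 + DE) / 24] and power = Φ(6.9 / SE − 1.96). Power is 89.0% at ICC 0 and 88.1%, 86.7% and 84.4% at the three positive values.

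**Step 6: does a group-aware analysis work with so few groups?** For equal group sizes, the group-aware comparison can be approximated by setting exercise-arm group means against individual controls, with Satterthwaite degrees of freedom. In the same simulations (6 groups of 4), its type I error was 5.0-5.1% at every ICC.

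**The case against.** The strongest reply is that the harm is conditional. The documents give no ICC, and at 0 the ordinary regression is correct. Several described features would lower the correlation. The first 2 weeks are one-to-one, loads and starting level are set for each woman, all use one facility and one periodised programme, and missed sessions can be moved to another day, so groups may mix. Primary outcome assessors are blinded. This all stands. It favours the lower figures, but it does not establish that the correlation is zero after 20 group sessions.

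Second, a reader might infer that trainers are shared within fixed groups. The article does not give the number of trainers, their assignment to groups, or whether membership is fixed. That inference is plausible but unsupported.

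Third, because women are randomized individually, a null in which training changes nobody's outcome keeps the ordinary test at 5% however the groups are formed. The inflation applies to a different null, in which groups or trainers do shift outcomes and the shifts average to zero. This is correct and limits the type I error claim. The interval is still too narrow whenever real group effects exist.

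Fourth, the article is condensed, and naming linear or quantile regression does not rule out cluster-robust errors specified elsewhere. That is fair. However, section 2.9 does list its sensitivity analyses, and none concerns training group.

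**Conclusion.** The point holds in a conditional and modest form. Grouping in one arm is part of the stated design, and the regression and sensitivity analyses as described leave it unaddressed. If the exercise-arm ICC lies between 0.02 and 0.10, the type I error is about 5.3% to 6.7% and the correct interval is about 1.5% to 7% wider. This assumes 1:1 allocation, a two-sided test and about 6 groups of 4 analysed women.

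A reader might go further and conclude that the intervals are too narrow and the error rate above 5% as a matter of fact, for every outcome. The documents do not support that, because both statements require a positive ICC that is nowhere given. A required sensitivity analysis is a proportionate response. Making the nested model primary would be a trade-off, since the group variance would be estimated from very few groups.

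**What to change.** - Record each exercise-arm woman's phase-2 training group and lead trainer. The tally sheet (Table S3) is not shown and may already do this.
- Add to section 2.9 a required sensitivity analysis of the primary strength outcomes, using a partially nested linear mixed model. It has a random group effect in the exercise arm only, controls as singletons, group taken as first assigned in phase 2, and Satterthwaite or Kenward-Roger degrees of freedom.
- Report the ICC with its interval. Qualify the conclusion if this model's interval and that of the ordinary regression lead to different conclusions.

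The cost is at most these two identifiers and one extra model. The downside is a slightly wider, somewhat conservative interval and an ICC estimated imprecisely from about 5-7 groups. The model has no direct counterpart for an outcome analysed by quantile regression, so for such an outcome it should be presented as a check on the mean difference.

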**Table 1 T1:**

Periodization of the supervised resistance training program.

Each supervised exercise session consists of 3 parts. Part 1 is a preparatory part of approximately 15-20 minutes, divided into 5 minutes of low-intensity aerobic activity (50%–65% of the heart rate reserve) either on a treadmill o an elliptical trainer, 2 thoracic mobility exercises and 2 central stability (CORE) exercises (5-8 minutes), 2 scapulohumeral joint stability and 2 dynamic stability exercises (5-8 minutes). The exercise intensity for part 1 will be 3/10 quantified through the OMNI perceived exertion scale for resistance exercise (OMNI-RES).^[41]^ Part 2 (ie, the main part) comprises a circuit of 4 dynamic resistance exercises (ie, bilateral dead lift, bilateral seated row, bilateral squat, and bilateral seated bench press). Resistance training intensity will be equivalent to 40% to 70% of 1 repetition maximum (1 RM) and will be individually calculated so that participants progressively work with a training load that can be lifted 24 times (ie, 24 RM) to a training load that can be lifted 12 times (12 RM). Progressions will generally occur weekly. Although 60% to 70% of 1 RM is recommended in healthy adults to improve strength,^[42]^ previous research has shown that more moderate intensities (ie, 40%–60% of 1 RM) can improve muscular power, strength, muscular size, and functional tasks even in older people.^[43]^ Exercise intensity will be individually quantified through the character of the effort (CE; which represents the number of repetitions actually performed out of the maximum number of repetitions that could be performed with a given load), as previously reported,^[44,45]^ and participants will be asked to report their subjective level of effort (ie, after each exercise) through the OMNI-RES.^[41]^ The CE will be distant from muscle failure to maximize strength^[46]^ gains^[47]^ and minimize risks. According to previous research,^[48,49]^ in each set, participants will perform half of the maximum number of possible repetitions to achieve greater mean repetition velocity, lower impairment of neuromuscular performance, faster recovery, reduced hormonal response and muscle damage, and lower reduction in heart rate variability.^[48,49]^ For greater strength gains, participants will be advised to perform the concentric phase of each exercise at maximum voluntary velocity.^[43,50]^ The resting periods between sets of the same exercise will be of approximately 3 minutes as recommended in older adults.^[43]^ Part 3 consists of a collective calm-down, including dynamic/static stretching of major muscle groups (ie, pectoralis major, dorsal width, quadriceps, hamstrings), and a general group evaluation of the session (Table S3). The main exercises that are to be performed along the exercise program, divided by part of the session, are presented in Table 2.

**Table 2 T2:**
[figure not shown]
Exercises that are to be performed along the resistance training program^∗^.

All participants will be instructed to report any difficulties, limitations or needs so that the intervention can be adapted to individual needs. To maximize adherence, participants will be sent motivational messages (ie, either through WhatsApp or email) every 2 weeks, and participants who miss sessions will be contacted to ask for reasons and reallocate the schedule to undertake the session another day. Adherence to the program will be reported as the median attendance frequency and the proportion of patients attending ≥75% (ie, 18 sessions; the minimum pre-defined attendance to assess efficacy). Adherence to the exercise program, potential adverse events, and other relevant information will be measured throughout the whole intervention period using a comprehensive tally sheet to be completed daily by the PT during and after each training session. The detailed tally sheet to be used in this study, based on a previous well-designed exercise protocol,^[51]^ is shown as additional file (Table S3). There will not be any nonexercise component in this intervention.

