#### Control group

2.6.2

Participants assigned to the CG will be required to undertake aerobic activity by performing a minimum of 10,000 steps per day to meet the physical activity guidelines but will not be involved in supervised resistance training. We thus aim to guarantee that all enrolled participants benefit from being physically active as they are all required to comply with aerobic activity recommendations. Compliance with the step goal will be monitored through the Z11 Smart Band (Smart&Sport, Shenzhen, China) activity bracelet in the same way as the EG. For ethical reasons, the CG will have the possibility to undertake the resistance exercise intervention once the trial finalizes.

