### Data collection procedure

2.8

Baseline (ie, from September 9 to September 20, 2019) and follow-up (from December 16 to December 20, 2019) evaluations will be performed at the Exercise Laboratory of the University of Almería. Each participant begins filling out online questionnaires including health-related quality of life, cancer-related fatigue, depression, life satisfaction, and a general sociodemographic questionnaire. Thereafter, body composition is assessed in a private room, followed by shoulder joint mobility and presence of lymphedema, upper- and lower-body muscular strength and cardiorespiratory fitness.

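### Adverse events are recorded by a method that works only in the exercise arm, so their counts could not be compared between arms

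*Protocol article*

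**What the plan says.** Adverse events are dealt with in section 2.6.1 (Experimental group), after Table 2. Besides adherence, the article states that "potential adverse events, and other relevant information will be measured throughout the whole intervention period", and it names the instrument: a "comprehensive tally sheet to be completed daily by the PT during and after each training session".

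The same section sets out the exercise arm's contact with trainers. Participants "will carry out 2 strength training sessions weekly for 12 weeks", so that "the program comprises a total of 24 training sessions". They are also asked to do "home-based aerobic training consisting in meeting the physical activity guidelines of 10,000 steps per day".

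Section 2.6.2 (Control group) says that control women are "required to undertake aerobic activity by performing a minimum of 10,000 steps per day" and "will not be involved in supervised resistance training". The one form of monitoring it names is the activity bracelet for steps, applied as in the exercise arm.

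Adverse events are not among the outcomes in section 2.7. Section 2.8 describes the assessment visit: "Each participant begins filling out online questionnaires including health-related quality of life, cancer-related fatigue, depression, life satisfaction, and a general sociodemographic questionnaire", followed by the physical measurements. Section 2.9 describes no analysis of adverse events.

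**The concern.** A comparison of adverse events between randomised arms is fair only if both arms are asked in the same way and equally often. Here the stated method fixes the content, the period, the instrument, the recorder and the timing, and all of these depend on sessions that one arm does not have. Control women are not unexposed: the trial assigns them a daily walking target too, and the article states no means of recording an injury or symptom that arises from it.

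At stake is what the trial can say about the safety of adding resistance training. A table of recorded events by arm would show an excess under exercise even if the true risks were equal. The Discussion hopes that the results will help develop exercise prescription for breast cancer survivors, and a fair account of harms is part of that. The strength, fitness and quality-of-life comparisons are not touched.

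**Working it through.** **1. Recording occasions, exercise arm.** Inputs from section 2.6.1: 2 sessions a week for 12 weeks.

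- 2 × 12 = 24, which reproduces the article's own total.
- By phase: 2 × 2 = 4 individual sessions in weeks 1–2 and 2 × 10 = 20 group sessions in weeks 3–12; 4 + 20 = 24.

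With one tally sheet per session, each exercise participant has up to 24 occasions, fewer if she misses sessions.

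**2. Recording occasions, control arm.** Input from section 2.6.2: no supervised sessions, hence no trainer and no sheet. Occasions: 0.

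**3. Other routes stated in the article.**

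| Route | Section | Serves control-arm adverse events? |
|---|---|---|
| Participants told to report difficulties, limitations or needs | 2.6.1 | Not clearly: it sits in the exercise-arm section and its purpose is to adapt the intervention |
| Contact after a missed session | 2.6.1 | No: only the exercise arm has sessions |
| Bracelet | 2.6.2 | No: records steps |
| Arm volume and lymphedema, baseline and week 12 | 2.7, 2.7.2.10 | Yes for this one harm, identically in both arms |
| Reasons for abandonment | 3.1 | In part: not limited to one arm, but only for women who leave |

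Apart from measured arm swelling and reasons for leaving, no stated route reaches control women.

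**4. Direction and possible size.** The article gives neither an event rate nor a capture share, so this is illustration only. Assume the same true risk *p* in both arms, a capture share *e* in the exercise arm and *s* in the control arm. Then

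apparent risk ratio = (p × e) / (p × s) = e / s.

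The ratio exceeds 1 whenever e > s, whatever *p* is. With e = 1:

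| Control capture *s* | Apparent risk ratio when the true ratio is 1 |
|---|---|
| 1.00 | 1.0 |
| 0.75 | 1.33 |
| 0.50 | 2.0 |
| 0.25 | 4.0 |
| 0 | undefined (no control events) |

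In counts, assuming 30 women per arm (half of the planned 60), p = 20%, e = 1 and s = 0: 30 × 0.20 = 6 events against 0, a spurious difference of 20 percentage points. With p from 10% to 30%, the counts run from 3 to 9 against 0, and the spurious difference from 10 to 30 points. At s = 0.5 and p = 20% the counts are 6 against 3, a difference of 10 points.

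A value of *e* below 1 shrinks the ratio in proportion. The direction stays the same as long as the exercise arm's capture is the higher, which is what 24 occasions against 0 leads one to expect.

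**The case against.** The strongest reply is that the sentence describes session monitoring within a section written to an exercise-reporting template. It does not say that the tally sheet is the trial's sole source of adverse-event data. The article states that it follows SPIRIT and has ethics approval, and a fuller protocol, not shown, may hold a trial-wide procedure. The questionnaire list in section 2.8 proves little, since it is introduced as a partial list and omits the upper-limb disability questionnaire that section 2.7.2.4 names. Finally, neither the aims nor section 2.9 plans a comparison of adverse events.

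Much of this stands. That no control-arm route exists is partly an inference from silence, and the absence of a planned safety comparison makes the point less serious. But the article does more than stay silent. It fixes how adverse events are measured over the whole intervention period, and that method cannot operate in the control arm. It states equal monitoring for steps and states none for adverse events.

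A reader might infer three stronger things that the documents do not support:

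- *Events during home walking are lost in both arms.* For the exercise arm this does not follow. The sheet is meant to cover the whole period and other relevant information, trainers see the women twice a week, and missed sessions prompt a contact. Events between sessions may be noted at the next one. The article does not say that they are asked about, and the sheet's content (Table S3) is not at hand.
- *Arm swelling is missed.* It is not: arm volume and lymphedema are assessed in both arms at baseline and week 12.
- *The distortion can be put at a risk ratio of at least 2, because recording covers about 1% of the time.* Sessions do occupy 24 h of 84 × 24 = 2,016 h, or 1.2%, but that is when the form is filled in, not the period it covers. The figure also conflicts with the near-complete exercise-arm capture on which such a ratio depends. A ratio of 2 or more further requires control capture of 50% or less; at 75% it is 1.33.

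**Conclusion.** The point holds in a limited form. The only adverse-event recording described gives up to 24 occasions per exercise participant and none per control participant, while both arms carry the same daily step target. Recorded events would fall mainly in the exercise arm whatever the true risks, so their counts could not be compared between arms.

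The direction rests on one assumption: that fewer control-arm events would surface without any stated enquiry than exercise-arm events with one. The size is unknown, and the ratios and counts worked out above are illustrations, not estimates.

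It would go too far to say that harms cannot be compared at all. Lymphedema and arm volume are measured equally, and reasons for abandonment are to be reported. The conclusion also depends on the article alone: if the full protocol already holds an identical enquiry for both arms, the remaining task is to state it.

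**What to change.** Add one short adverse-event form, identical in wording and timing, to the week-12 online questionnaires that both arms already complete. It should ask about events since baseline and name explicitly those between sessions and during home walking. Suitable items are new or worse musculoskeletal pain or injury, arm swelling, unplanned medical contact and hospital admission.

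State that any between-arm comparison of adverse events will rest on this form, alongside the measured arm-volume and lymphedema outcome. Report the trainer tally separately, as descriptive data for the exercise arm.

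The cost is a few minutes per participant and one extra page in an existing online set. The main weakness is recall error over 12 weeks. It could be reduced by sending the same form in a short message every two weeks, provided it goes to both arms on the same schedule. Treatment, eligibility and the primary outcome are unchanged.
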